### Adverse event monitoring and reporting

All adverse events will be carefully monitored at every level of the FITonICU study. A Data Safety Monitoring Board provides oversight and meets after randomisation of every 20 newly recruited patients. All adverse events are reported immediately to the responsible physician and the board members are informed of all adverse events.

The Data Safety Monitoring Board and the research team (all authors) will be responsible for data safety and for the confidentially of recruited patients. The confidentiality of participants will be granted by using anonymous ID lists for all recruited patients. All patient data will be maintained and stored confidentially on a separate computer server.

The Data Safety Monitoring Board will do an interim analysis for safety of every 20 included and treated patients. The trial will be stopped:If there is a statistically significant difference in safety between the groups in one direction at an alpha level of 0.05 at this time point of recruitmentIf one of the interventions is associated with unexpected excessive adverse effects such as skin ulcerations, pulmonary embolism or deep vein thrombosis, or there are excessive withdrawalsIf the study recruitment is unsuccessful (e.g. 3 months without any recruitment) orIf other situations occur that might justify stopping this trial

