### Assessment of safety and adverse events

At each assessment the following parameters will be systematically recorded: recurrent, fatal or nonfatal cardiovascular or cerebrovascular events; referral to an acute hospital; and death. After each intervention, the treating physiotherapist will record the presence of self-reported pain, fatigue, dizziness and number and nature of falls, and note any other adverse events. Additionally, oxygen saturation, mean arterial pressure, and heart rate will be documented for every therapy session.

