### Sample size

Until now, no trials and, therefore, no specific effect size of the selected interventions for this specific population are present in the peer-reviewed literature. Our sample size calculation of 45 patients per study arm is based on a difference of 6 points in the primary endpoint of the FSS-ICU sum score between the parallel groups after 2 weeks of treatment. We assume an alpha level of 5%, a statistical power of 80% (beta = 20%) and a standard deviation (SD) of 10 using a two-sample *t* test for mean differences. Our assumption is based on the theory that the one experimental group achieves a mean of 22 points and the other group achieves a mean of 16 points in the FSS-ICU test assuming a SD of 10 in the FSS-ICU sum score and assuming that the rate of recovery of walking ability will be 0.6 in the one and 0.4 in the other group. We used the SAS (SAS Institute Inc., Cary, NC, USA) power and sample size programme for our sample size calculation. Because we consider a 20% dropout rate, a total of 108 patients (54 per study arm) would be enrolled to ensure 45 subjects in both intervention arms.

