### Statistical methods

We will conduct both intention-to-treat and per-protocol analyses, with the intention-to-treat analysis being always the primary analysis for the primary and secondary outcomes.

Our descriptive statistics will include means and SDs, medians and interquartile ranges for continuous variables, and the number and proportions for categorical variables as appropriate [39].

We will compare the two intervention groups at baseline regarding characteristics and demographics, using two-tailed Student’s *t* tests or Fisher’s exact tests, as appropriate. Variables that differ between the groups at baseline will be considered as possible confounders and adjusted for in subsequent analyses. The global alpha level will be set at 0.05 for all comparisons. To avoid multiplicity we will use a Tukey-Kramer alpha adjustment for multiple comparisons of the same outcome. Skewed data will be analysed with nonparametric test alternatives (e.g. we will use the Mann-Whitney *U* test instead of Student’s *t* tests if data are skewed).

For the primary endpoint, the FSS-ICU, we will test the hypothesis that the sum score after 2 weeks of intervention and at follow-up will be statistically different between groups. We will consider a minimum difference of 5 points of the FSS-ICU sum score (range 0–35 points) between groups as being clinically important.

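### The safety rule makes an unadjusted p<0.05 a mandatory stop at each of about five looks, so equally safe arms carry roughly a 13–14% chance of a false stop on one measure by a large-sample test

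*Protocol article*

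**What the plan says.** Under Adverse event monitoring and reporting, the protocol article gives the timing of the looks: "The Data Safety Monitoring Board will do an interim analysis for safety of every 20 included and treated patients". It then gives the consequence: "The trial will be stopped:If there is a statistically significant difference in safety between the groups in one direction". The criterion in full is a "statistically significant difference in safety between the groups in one direction at an alpha level of 0.05", judged at that point of recruitment. The same list has three further grounds for stopping: unexpectedly excessive adverse effects or withdrawals, failed recruitment, and any other situation that might justify it.

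Under Sample size, planned enrolment is 108 patients, 54 per arm: "Because we consider a 20% dropout rate, a total of 108 patients (54 per study arm) would be enrolled".

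Assessment of safety and adverse events lists what is recorded. At each assessment these are "recurrent, fatal or nonfatal cardiovascular or cerebrovascular events; referral to an acute hospital; and death". After each session they are pain, fatigue, dizziness, falls and other adverse events, and three physiological readings are documented for every session. The article does not say which of these, or what combination, makes up the safety difference in the stopping rule.

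The only multiplicity method named, under Statistical methods, is a Tukey-Kramer adjustment for repeated comparisons of one outcome. It is not linked to the safety looks and is not a group-sequential boundary.

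**The concern.** A test at 0.05 has a 5% false-positive rate when it is done once. Done repeatedly on accumulating data at the same level, the chance of at least one significant result rises with every look. Here each such result is tied to an obligatory action: the wording leaves the board no room to judge that an isolated p just under 0.05 is chance.

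At stake is an early end to a single-centre trial for a reason that may be chance. The 80% power assumes 45 evaluable patients per arm and makes no allowance for such a stop. The level, the timing and the binding consequence are all stated in the article, so this is not detail left for an analysis plan.

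**Working it through.** **Inputs from the protocol article.** Looks every 20 patients; 108 enrolled; 1:1 allocation; 0.05 at each look; mandatory stop. The phrase "between the groups in one direction at an alpha level of 0.05" could mean a one-sided 0.05 or a two-sided 0.05 with either arm worse, so both were computed.

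**Assumed, because not given.** Event rates of 2–50% per patient, equal in both arms; 10 patients per arm added between looks; cumulative data at each look.

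**The sample size that sets the number of looks.** A difference of 6 points, SD 10, two-sided 0.05 and 80% power require 44.6 per arm by the t test, hence 45 as stated. The total follows as 45 × 1.2 = 54 per arm, and 2 × 54 = 108.

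**Number of looks.** 108 / 20 = 5.4, so looks fall at 20, 40, 60, 80 and 100.

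**One measure, large-sample test.** Let Z_k be the cumulative test statistic at look k. With no true difference, Z_k = (X_1 + … + X_k)/√k, where the X are independent standard normal. The false-stop chance by look k is the probability that some |Z_j| > 1.96 for j ≤ k (or Z_j > 1.645, one-sided). By simulation:

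| Looks done | Two-sided 0.05 | One-sided 0.05 |
|---|---|---|
| 1 | 5.0% | 5.0% |
| 2 | 8.3% | 8.0% |
| 3 | 10.7% | 10.1% |
| 4 | 12.6% | 11.7% |
| 5 | 14.2% | 13.0% |

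**One binary event.** Exact binomial recursion with 10, 20, 30, 40 and 50 patients per arm, stopping at the first two-sided p ≤ 0.05. False-stop chance over five looks:

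| Assumed event rate | Fisher's exact | Chi-square |
|---|---|---|
| 2% | 0.04% | 1.5% |
| 5% | 1.0% | 7.5% |
| 10% | 3.6% | 11.9% |
| 20% | 6.6% | 13.2% |
| 30% | 7.3% | 13.5% |
| 50% | 7.6% | 14.0% |

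**The first look alone (10 per arm).** Fisher's test gives p = 0.087 for 4 events against 0 and p = 0.033 for 5 against 0. Over the rates tried, the false-stop chance at this look is at most 1.3% by Fisher and 4.2% by chi-square. The risk therefore comes mostly from the accumulation of looks, not from the first 20 patients.

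**The case against.** The best defence is that safety monitoring may properly accept more false alarms than efficacy testing, because a missed harm costs more than a needless pause. This stands as an argument for a sensitive alarm. It does not support an automatic stop: the same p<0.05 can alert the board just as early without ending the trial.

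A second defence is that the risk may be small. If the board tests one uncommon serious event by Fisher's test, it is about 1% or less at rates up to 5%. This also stands. But the article names Fisher's test only for baseline comparisons and fixes neither the event nor the test for this rule. The low event rates it reports (0.2% over 541 in-bed cycling sessions; no adverse event in 10 pilot patients) do not settle per-patient rates for symptoms.

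Third, a stop at the fifth look costs little, with 100 of 108 patients recruited, and patients already treated still contribute two-week data. That is correct, and is why the four-look figure is also given.

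Three stronger readings are tempting, but the documents do not support them:

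- *Every recorded measure is a stopping test.* The article says what is recorded, not that each item is tested. Large-sample figures for several measures (33–37% for three, 57–71% for eight, at correlations from 0.5 to 0) show only how the risk would grow if it were so.
- *The rule contradicts the overall significance level.* The sentence "The global alpha level will be set at 0.05 for all comparisons" stands under Statistical methods and concerns the outcome comparisons. Stopping for harm makes no efficacy claim and does not inflate that error rate.
- *The trial would be likely to end at 20 patients.* The first-look figures above do not bear this out.

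**Conclusion.** The concern holds in a limited form. As written, the rule forces a stop at any of about five looks on an unadjusted 0.05. For one measure with equally safe arms, the false-stop chance is 13.0% (one-sided) to 14.2% (two-sided) by a large-sample test, nearly three times the nominal level. For one binary event it ranges from below 0.1% to about 8% by Fisher's exact test and from about 1.5% to 14% by chi-square.

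These figures assume cumulative testing, equal group sizes at each look and, for the binary case, event rates of 2–50% that the article does not supply. Where the true value lies depends on the measure and test, which the article leaves open. The fault is the combination of a per-look 0.05 with a binding consequence, not the board's frequent inspection of safety data. It merits correction, but it does not invalidate the design.

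**What to change.** For this criterion only, replace the obligation to stop with a statement that a nominal p<0.05 for a safety difference at any look triggers review by the Data Safety Monitoring Board, which then makes a non-binding recommendation. Add that 0.05 is a per-look level not adjusted for repeated looks. Leave the other grounds for stopping unchanged; they already allow a stop for excessive adverse effects or any other justifying situation, so no protection is lost.

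A stricter formal boundary is not required. It would reduce false stops, but would also make the limit slower to register real harm, a trade-off for the sponsor and the board.

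The cost is a short amendment to the stopping paragraph and to the board's instructions, with no change to patient procedures or sample size. The one small downside is that stopping on this criterion would then rest on the board's judgement.

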### Randomisation and concealment of allocation

Each study participant will be randomly assigned to one of two intervention groups, either the MOBILITY group or the BEDCYC group. Allocation will be concealed within an opaque sealed envelope (Fig. 2). The computer-generated random allocation sequence list will be carried out (JM) using a random-number generator (randomizer.org). Assignments will be enclosed in sequentially numbered, opaque, sealed envelopes and stored at the central study centre. The persons who assess eligibility, obtain informed consent and enrol patients in the trial ([name]) have no knowledge of group assignment. After recruitment, the appropriate numbered, opaque, sealed envelope will be opened and the randomisation information will be given to the patient and therapists (but not to the outcome assessors and not to the statistician performing the analysis).

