### BEDCYC

The BEDCYC group will receive, in addition to standard treatment, 20 min of in-bed cycle ergometer sessions (the same number, frequency and treatment time as the MOBILITY group) [22]. We chose in-bed cycling as comparator to compare two true active and potentially effective interventions. For instance Kho et al. recently described the feasibility and safety of in-bed cycle ergometry as part of routine ICU practice [22]. They described 181 patients on ICU receiving a total of 541 cycling sessions and described a very low (0.2%) event rate and concluded that the use of in-bed cycling as part of routine physical therapy interventions in ICU patients is feasible and appears to be safe [22]. We will use the same in-bed cycle therapy approach as described earlier; however, contrary to the CYCLE pilot protocol of Kho et al. [37] we will use 20-min in-bed cycle ergometer sessions instead of 30-min sessions. BEDCYC will be provided by two experienced therapists who are only providing BEDCYC therapy but not the therapy to the experimental group.

Adherence to the BEDCYC therapy will be documented in daily logs and reported.

To control for cointerventions (standard therapy) during the intervention phase of the study (T0 to T1) therapists will document the total duration and content of both standard and additional therapy. Content will be described for each 5-min block.

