### Additional information

The standard care/treatment includes sitting balance exercise, stretching, positioning, sit-to-stand training, transfer training to get out of bed, strengthening exercise (in and outside of bed), stepping and assistive standing exercises as described previously [38]. The standard treatment will be about 45 min daily of individual physical therapy and the duration of therapy will be kept equal in both intervention groups. Total time spent in rehabilitative therapy will be recorded by so-called usual care intervention logs to report the number of physiotherapy and occupational therapy sessions received in the first 2 weeks of the study (as part of the usual care treatment). Information about medication and treatment will be recorded at baseline. Length of stay in ICU and the time spent in post-acute ICU and in rehabilitation will be documented (in days).

As described above, physiotherapists will record in every session the presence of self-reported pain, fatigue, dizziness, number and nature of falls and note other adverse events. The adherence to standard care will be described in daily logs and reported.

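### The harms asked about at each assessment do not match the harms that can stop the trial, which leaves a risk of unequal ascertainment between the arms

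*Protocol article*

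**What the plan says.** The protocol article describes two ways in which harms are collected, and a separate set of harms on which the trial can stop.

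- **At each assessment** (Assessment of safety and adverse events), the systematic list is "recurrent, fatal or nonfatal cardiovascular or cerebrovascular events; referral to an acute hospital; and death".
- **After each intervention** (same section), "the treating physiotherapist will record the presence of self-reported pain, fatigue, dizziness and number and nature of falls, and note any other adverse events". The section Additional information repeats this for standard care: "physiotherapists will record in every session the presence of self-reported pain, fatigue, dizziness, number and nature of falls and note other adverse events".
- **Stopping** (Adverse event monitoring and reporting): the trial stops if an intervention is associated with "unexpected excessive adverse effects such as skin ulcerations, pulmonary embolism or deep vein thrombosis". It also stops if a safety difference between the groups reaches an alpha level of 0.05 when the board looks, which is after every 20 included and treated patients. The safety variable for that test is not named.
- **General statement** (same section): "All adverse events will be carefully monitored at every level of the FITonICU study". Events go at once to the responsible physician, and the board is told of all of them.

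Two further statements show who makes the session records. Under Randomisation and concealment of allocation, "the randomisation information will be given to the patient and therapists (but not to the outcome assessors". Under BEDCYC, "BEDCYC will be provided by two experienced therapists who are only providing BEDCYC therapy but not the therapy to the experimental group".

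**The concern.** Both stopping criteria compare the arms: one asks whether an intervention is associated with excess harm, the other tests a difference between groups. Such a comparison is sound only if events are looked for equally in both arms. The harms the plan itself names as reasons to stop are not the ones it asks about in a uniform way. The record that might catch them is made by people who know the allocation and, for BEDCYC, by a team that treats only that arm.

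Two errors are possible. A real excess could go unnoticed because nobody is prompted to ask, or a difference in how readily two teams write things down could look like a difference in harm. After T1 there is a further gap: walking ability is followed to 12 months, but no follow-up assessment asks about falls or skin injury. The final account of benefit and harm would then be better documented on benefit.

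**Working it through.** The plan gives no figure to reproduce on this point. The check is a comparison of the sections, followed by an illustration.

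**1. Which harm is named where**

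| Harm | Named as a stopping example | On the list at each assessment | Named in the session record |
|---|---|---|---|
| Skin ulceration | yes | no | no; open item only |
| PE | yes | not by name; covered if classed as cardiovascular, or if it leads to acute-hospital referral or death | no; open item only |
| DVT | yes | as for PE | no; open item only |
| Falls | no, but could enter the unnamed safety variable | no | yes |

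Only skin ulceration is both a named stopping harm and clearly absent from the assessment list. PE and DVT are ambiguous. Falls are asked about only by treating physiotherapists.

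**2. Who records.** The assessment list belongs to visits carried out by blinded assessors. The session record belongs to therapists who know the allocation, with a dedicated pair for BEDCYC. Session content also differs: MOBILITY includes standing, stepping, walking and stairs, while BEDCYC is done in bed. Falls noted around the additional sessions therefore partly reflect what each session involves.

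**3. When.** Table 2 carries the walking scale (FAC) and the functional score (FSS-ICU) through 12 months. It has no row for falls or skin injury, and the assessment list does not add them at FU1, FU2 or FU3.

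**4. How much unequal capture could matter.** The documents give no event rates and no capture rates, so those below are assumptions.

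- Looks: every 20 of 108 patients gives 5 looks (20, 40, 60, 80, 100), taken as 10, 20, 30, 40 and 50 per arm.
- True event risk p is equal in the two arms. One arm records every event; the other records a fraction s. New recorded events per look are Binomial(10, p) and Binomial(10, p × s), accumulated over looks.
- Test: two-sided Fisher's exact test below 0.05 at any look; 20,000 simulated trials per scenario.

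| True risk p, both arms | s = 100% | s = 75% | s = 50% |
|---|---|---|---|
| 10% | 3.4% | 4.2% | 8.3% |
| 20% | 6.5% | 10.7% | 25.7% |
| 30% | 7.2% | 15.2% | 42.3% |

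The s = 100% column already contains the effect of five looks, so the rise across a row is due to unequal capture alone. At p = 20% and 50 per arm, the expected recorded counts are 50 × 0.20 = 10 against 10 × 0.75 = 7.5 or 10 × 0.50 = 5.

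At the first look, 5 against 0 recorded events is enough: p = 2 × C(10,5)/C(20,5) = 2 × 252/15,504 = 0.033. With 4 against 0 it is 2 × 210/4,845 = 0.087. A few unrecorded events can therefore decide the result. The opposite error, a true excess hidden by under-recording, was not simulated.

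**The case against.** The strongest reply is that the board's information is not confined to the assessment list. All adverse events are to be monitored, reported at once to the responsible physician and passed to the board, whatever their type. The stopping harms are examples of unexpected effects, and open-ended reporting is the usual way to catch those. Both arms use the same session items, and therapists giving these interventions cannot be blinded. Detailed adverse event forms may sit in the full protocol, which is not shown.

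Much of this stands, and it limits the point. Three stronger readings are tempting, and the documents do not support them:

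- *That all three named harms are off the list.* PE and DVT can reasonably be read as cardiovascular events, and a serious case may also appear as referral or death.
- *That the board's rule does rest on incomplete, arm-dependent reporting.* Nothing in the article shows that the two teams report differently. The design leaves room for it and no more.
- *That the gap can be sized from the 10 × 20 = 200 minutes of additional therapy.* Additional information extends recording to every physiotherapy session, with standard treatment of about 45 minutes daily, and a fall noted at a session need not have happened during it.

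What remains is that the general statement says what happens to an event once it is known, not how it comes to be known. A harm named in advance as a reason to stop can also be asked about in advance. Nor is this only a matter of omitted detail: the article prints a specific systematic list and a specific set of stopping harms, and they do not match.

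**Conclusion.** The concern holds in a limited form. The systematic list omits skin ulceration and falls and includes PE and DVT only by interpretation. The remaining prompted record comes from therapists who know the allocation and differ by arm, and no follow-up assessment asks about falls or skin injury. This is a risk of unequal ascertainment in the comparison the board makes, not a demonstrated bias.

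Its size cannot be taken from the documents. Under the assumed rates it runs from negligible (3.4% to 4.2% at a 10% risk and 75% capture) to serious (7.2% to 42.3% at a 30% risk and 50% capture). The conclusion assumes that the full protocol does not already prescribe uniform prompts for these harms; if it does, only the mismatch in the printed lists is left. The change is worth making because it is cheap and uses visits that already take place.

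**What to change.** In Assessment of safety and adverse events, add four items to the list recorded at T1, FU1, FU2 and FU3: skin ulceration, DVT, PE, and falls since the last assessment wherever they occurred. Use the same written definitions and prompts in both arms.

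To protect blinding, choose one of two routes. Either the responsible physician, who already receives all adverse event reports, completes the items; or the assessor asks the patient or ward staff, but only after FAC and FSS-ICU have been scored and without opening the therapy logs, which could reveal the allocation.

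Give these counts to the board alongside the therapists' notes. The stopping criteria themselves need not change.

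The cost is four more case report form items and a few minutes at existing visits. A small unblinding risk remains if a patient mentions the circumstances of an event; scoring first limits it for that visit, but not for later ones.
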